### Recruitment

Within each country, participating sites can have different recruitment functions including simply promoting the study and referring clients to a central service for recruitment or being a community-based recruitment site. The study will be promoted through promotional posters and flyers at the study sites and by outreach workers from study sites who will distribute promotional materials and discuss the study with potential participants, and provide facilitated referral into the study site in Armenia.

### Participant eligibility

Interested individuals will be screened for eligibility prior to referral to a clinical service.

Study inclusion criteria for participants are as follows:

Aged 18 years or older.Be attending a listed referral needle/syringe programme site or self-report ever injecting drugs.Must not be currently on or previously had treatment for hepatitis C.Be able and willing to provide informed consent in the local language.Be a citizen of the country (Armenia and Georgia—citizenship is not an inclusion criteria for Tanzania).Self-report not living with HIV (Georgia only).

Exclusion criteria are as follows:

Women known to be currently pregnant or who are breastfeeding.Individuals currently engaged in hepatitis C treatment.Unable to provide informed consent.Individuals diagnosed with a current hepatitis B infection or uncontrolled/newly diagnosed HIV infection (HIV controlled infection defined as clinically stable and on treatment for at least 12 months).Individuals with suspected tuberculosis infection or on preventive tuberculosis therapy (Tanzania only).Individuals with evidence of decompensated cirrhosis of the liver.Individuals with other significant comorbidity that requires specialist management of hepatitis C treatment (eg, renal dysfunction).Unable to cease taking contraindicated medicines for DAAs.

All participants will be given details of the study via the patient information sheet and be required to provide written consent prior to enrolling in the study. The participant information sheet is provided in local language (Armenian, Georgian and Tanzanian Swahili) and will be verbally explained to potential participants by delegated study staff obtaining consent.

### Intervention

This study will implement two comparison intervention arms and no control arm, as shown in figure 2. Final recruitment, retention and outcome assessments will be presented in accordance with the Consolidated Standards of Reporting Trials (CONSORT) statement, including CONSORT diagrams. Arm 1 will implement a rapid POC antibody test, in addition to on-site venipuncture for confirmatory RNA testing and pretreatment workup investigations during the initial baseline visit; treatment initiation will occur at the second visit. Arm 2 will implement a rapid POC antibody test and same-day treatment for all participants who test antibody positive at 5 min at the baseline visit. They will have on-site venipuncture for confirmatory RNA testing and other clinical investigations, and the decision to continue or cease treatment based on RNA test results will occur at the second visit. All eligible participants will be offered SOF (400 mg)/VEL (100 mg), to be self-administered orally once per day for 12 weeks. All POC antibody tests will be sourced and funded by the study sponsor Médecins du Monde. The manufacturer differs by country; details are provided in online supplemental material 1.

**Figure 2 F2:**
[figure not shown]
Arm 1 and arm 2 study procedures. DAA, direct-acting antiviral; HCV, hepatitis C virus; RDT, rapid diagnostic test; SVR, sustained virological response.

All study data will be recorded in clinical case report forms (CRFs) specific to the visit.

#### Arm 1 study procedures

##### Visit 1: enrolment, laboratory investigations, physical examination and medical history taking

Eligible participants enrolled in the study will have a OraQuick rapid hepatitis C antibody test using a fingerstick specimen, according to the manufacturer’s instructions, with the result documented at 20 minutes. In addition, the OraQuick rapid test result for the first 5 min will be documented at 1 min intervals, including with a photograph to record whether the test is reactive or non-reactive at that time point. The exact time at which the test first turns reactive will also be recorded. The result at 20 min will be provided to the participant. If the antibody result is negative, confirmatory testing will not be offered and the participant will exit the study with no further investigations performed. If the antibody result is positive, blood samples will be collected for confirmatory laboratory RNA testing and additional pretreatment investigations including complete blood count (platelets, haemoglobin), liver function tests (alanine aminotransferase (ALT), aspartate aminotransferase (AST), albumin, bilirubin) and renal function tests (serum creatinine±estimated glomerular filtration rate (eGFR)). The FIB-4 score will be calculated and used to determine cirrhosis status.

In addition, additional rapid tests will be conducted at baseline visit:

HIV antibody 1/2 RDT using venous blood sample.Hepatitis B surface antigen (HBsAg) RDT using venous blood sample.Urine dip-stick pregnancy test for all female participants with childbearing potential aged 18–49 years (pregnancy test can also be completed as part of pretreatment laboratory investigations in arm 1).

The brands of HIV and HBsAg RDTs will be included in online supplemental material 1; brands differ by country, depending on national procurement.

In Tanzania and Armenia, those who return a non-reactive HBsAg RDT and have no evidence of prior hepatitis B vaccination will be offered vaccination through the study. Evidence of vaccination is sourced through medical records accessible by study sites. In Georgia, those eligible for vaccination will be referred to a newly established national programme for vaccination.

Those newly diagnosed with HIV will be referred to treatment and be allowed to represent for study participation once their HIV is clinically stable, if recruitment is still open at that time in Armenia and Tanzania.

###### Physical examination, medical history and drug-drug interactions

Participants will undergo physical examination to exclude suspected decompensated cirrhosis (portal hypertension, variceal haemorrhage and hepatic encephalopathy, coagulopathy or liver insufficiency, palmar erythema, nasal bleeding and oedema). Participants will have their medical history taken and current medications/supplements recorded.

Any participants with suspected decompensated cirrhosis or other comorbidity that may exclude the participant from this study will be referred to a specialist for further review and care.

Drug-drug interactions with SOF/VEL will be assessed using the Liverpool Drug Interactions online resource (Liverpool HEP Interactions) and any amber/red drug-drug interactions must be resolved with input from the participant and other treating/prescribing clinician(s) to assess appropriateness of ceasing/altering these treatments before DAA can be initiated.

The baseline participant questionnaire will be administered by study staff. This questionnaire collects information on demographic characteristics, history of incarceration, injecting practices, employment, income and productivity, healthcare utilisation, costs of attending for hepatitis C care and quality of life (EuroQol 5-Dimension 5-Level questionnaire(EQ-5D-5L) and EuroQol Visual Analogue Scale (EQ-VAS)).

### Visit 2: confirmatory laboratory results and treatment plan

Following receipt of the HCV RNA test result:

If the confirmatory laboratory HCV RNA result is negative, the study nurse/doctor will communicate this to the participant (via phone call or in person). The participant will exit the study here. Standard harm reduction messaging and window periods for detection of HCV will be discussed with the participant.If the confirmatory laboratory HCV RNA result is positive, the participant will be assessed for treatment eligibility based on other laboratory investigations.For assessment of liver cirrhosis, participant pathways are outlined per country in table 2.

**Table 2 T2:** Differentiated care pathways by Fibrosis-4 index (FIB-4) score result

FIB-4 score	Armenia	Georgia	Tanzania
<1.25	A FIB-4 score <1.25 indicates the individual is unlikely to have cirrhosis of the liver. Participants with a FIB-4 score <1.25 will be eligible to be prescribed SOF/VEL without further assessments.		
1.25–2.67	Participants will continue to start DAAs but can be referred for specialist review at the clinician’s discretion.	Participants with FIB-4 scores of 1.25–1.45 are considered to have ‘low fibrosis’ and will continue to start DAAs without further assessments at the study site. Participants with a FIB-4 score of >1.45–3.25 require FibroScan and review by a consulting specialist through case review of investigations with the study doctor, and if required, in-person appointment.	Participants will continue to start DAAs but can be referred for specialist review at the clinician’s discretion, in particular for ongoing monitoring.
>2.67–3.25	Participants will be reviewed by the supervising infectious diseases specialist and a decision about referral to a hepatologist will be made together with the treating study clinician.		
≥3.25	Participants with a FIB-4 score >3.25 must be referred to a hepatologist/gastroenterologist for further assessments prior to initiating treatment, given the higher risk of decompensated cirrhosis.		

DAA, direct-acting antiviral; SOF/Vel, sofosbuvir/velpatasvir.

In addition, the participant will be referred to a hepatologist/gastroenterologist if the participant’s laboratory results indicate any of the specified additional risk factors for decompensated cirrhosis (ALT or AST >200 U/L, bilirubin >1.14 mg/dL, albumin <3.5 g/dL without other obvious cause, or past/current jaundice, ascites, hepatic encephalopathy or haematemesis and melena).

If the specialist determines that the participant does not have decompensated cirrhosis, then they can receive DAA treatment as part of the study in arm 1 and will be followed up according to study timelines.

If the participant has elevated serum creatinine, the study doctor should calculate the eGFR. If eGFR is <30 mL/min/1.73 m^2^, they will be excluded from receiving DAA therapy as part of the study and referred for specialist review for ongoing care.

If the participant is deemed eligible for treatment, the study doctor will provide them with the first 4 weeks of SOF/VEL (28-day bottle) and ask them to begin treatment.

### Visit 3: treatment monitoring and dispensing

Participants will attend the study clinic between 0 and 7 days prior to week 4 of their treatment plan to collect the next 4 weeks (28-day bottle) or remaining 8 weeks (56-day bottle) of treatment, with number of weeks dispensed at clinician’s discretion.In Georgia, only 4 weeks of treatment will be dispensed at a time (as per national programme protocol).In Tanzania, 4 weeks of treatment will be dispensed routinely; however, 8 weeks of treatment will only be dispensed when the participant requests it and the clinician approves necessity.Participants’ self-reported adherence to treatment will be assessed. Any side effects and any adverse events will be documented.In the event of missed doses, additional weeks of treatment may be provided at the clinician’s discretion, in consultation with the Principal Investigator.

### Additional on-treatment monitoring and dispensing visits

For participants in Georgia, participants will attend the study clinic when they are due for the next 4 weeks of treatment to collect the next bottle. In addition, participants will receive a week 12 monitoring appointment.For participants in Tanzania, most participants will attend the study clinic between 3 and 7 days prior to week 8 of their treatment plan to collect the final 4 weeks (28-day bottle) of treatment at visit 4. In addition, participants will receive a week 12 monitoring appointment.For participants in Armenia, there will be no scheduled in-person appointment or laboratory monitoring during treatment between weeks 4 and 12, unless scheduled at the clinician’s discretion. Participants will receive a scheduled telephone call or in-person appointment at weeks 8–12 to assess treatment adherence and side effects, and to address any issues with lost medication.

### Treatment outcome assessment (SVR weeks 4–20)

Participants will attend the study clinic to have venous blood samples taken for RNA testing to confirm if they have achieved SVR post-treatment.Participants can be assessed for SVR anytime from ≥4 weeks post-treatment completion until 20 weeks post-treatment completion*.Participants will complete the interviewer-administered SVR participant questionnaire, covering similar domains to the baseline questionnaire.

SVR will be defined as ‘HCV VL <10 IU/mL’ or ‘HCV VL Not Detected’, if using GeneXpert HCV VL test/other quantitative test, and as ‘HCV RNA not detected’, as per laboratory procedures if using another HCV RNA test.

*In secondary analyses, if an RNA negative result is returned after 20 weeks, it will be categorised as achieving SVR. If a positive result is returned after 20 weeks, the participant will be categorised as ‘indeterminate SVR’, given the uncertainty regarding whether treatment was unsuccessful or the participant had been re-infected with hepatitis C.

### Study exit

Participants may exit the study at various time points: when they choose to withdraw from the study, when the clinician identifies a medical issue/ineligibility prompting participant withdrawal or when they have been identified as lost to follow-up due to no longer being contactable.

Throughout, there will be a minimum of three attempts over up to 3 weeks to contact participants to arrange the follow-up appointment if the participant misses the scheduled appointment. In the case of SVR, participants will remain in the study until the SVR20 time point passes; they will be contacted up to four times, every 4 weeks to attempt to arrange for SVR appointment.

### Arm 2 study procedures

#### Visit 1: enrolment, laboratory investigations, physical examination, medical history taking, drug-drug interactions review and presumptive treatment prescription

Eligible participants enrolled in arm 2 will undergo an OraQuick rapid hepatitis C antibody test using a fingerstick specimen as per arm 1. The result at 5 min will be provided to the participant as a preliminary result and used to inform whether same-day treatment is offered. This is the key difference between arm 1 and arm 2, with participants in arm 2 offered presumptive treatment based on this result at 5 min, without waiting for the RNA result.

Laboratory testing on a venous sample is then required to confirm whether the participant has current infection. If the antibody result is negative, confirmatory testing will not be offered and the participant will exit the study with no further investigations performed (as per arm 1).

If the antibody result is positive, blood samples will be collected for confirmatory laboratory RNA testing and additional investigations (as per arm 1). The FIB-4 score will be calculated and used to determine cirrhosis status.

If the POC result is positive at 5 min, blood samples will be collected for confirmatory laboratory RNA testing and additional investigations. Additional rapid tests, including HIV antibody 1/2 RDT, HBsAg RDT, rapid urine pregnancy tests, physical examination for signs and symptoms of decompensated cirrhosis, medical history taking and drug-drug interactions chart review for contraindications for same-day treatment will be conducted. Any participants with suspected decompensated cirrhosis or other comorbidity that may exclude participants from treatment in arm 2 of this study will be referred to a specialist for further review and care.If the POC result is a negative antibody test at 5 min and a positive test at 20 min, blood samples will be collected for confirmatory laboratory RNA testing and additional investigations, and the participant will be told that their test indicates they have been exposed to hepatitis C but may have a current infection. These participants are ineligible for same-day treatment in arm 2, but if their RNA test is subsequently positive, they will be offered treatment as per study procedures of arm 1 of the study but will not count towards the enrolment target.

Participants will be eligible for same-day treatment if they have:

No physical signs of decompensated cirrhosis.No comorbid conditions that require further investigation or referral to a specialist.No contraindicated medications (amber/red using online Liverpool Drug Interaction Checker).

If the participant is deemed eligible for treatment, the study doctor will provide 28 days of SOF/VEL and the participant will be asked to begin treatment. The blood sample for confirmatory RNA testing must be collected prior to providing any treatment medication. If there is an issue with the blood sample itself, the participant will be asked to return to the study site as soon as possible for a follow-up blood draw. Only after confirmatory RNA laboratory results will a second bottle of 28 SOF/VEL doses be provided for the participant to continue their treatment course.

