#### Visit 2: confirmatory laboratory results and treatment plan

If the confirmatory laboratory HCV RNA result is negative, the study nurse/doctor will contact the participant (via phone call immediately) and the participant will be asked to stop treatment immediately and to return unused DAAs either directly to the clinic or an outreach worker, or in some cases via a prepaid envelope provided to them in advance. This group of participants will be actively followed up for a face-to-face appointment to ensure they understand the test result and implications and to collect information on their experience of treatment. However, following this next visit, the participant will exit the study. Standard harm reduction messaging and window periods for detection of HCV will be discussed with the participant.If the confirmatory laboratory HCV RNA result is positive, the participant will be assessed for eligibility for treatment continuation based on other laboratory investigations. If a participant is eligible, the participant will continue treatment for a total of 12 weeks.

Participants returning laboratory investigations indicating renal dysfunction, with abnormally high levels of serum creatinine where eGFR <30, will be asked to pause treatment while they seek specialist review and advice on whether to continue treatment.

Participants returning laboratory investigations indicating cirrhosis (FIB-4 score >3.25; ALT or AST >200 U/L; bilirubin >1.14 mg/dL; albumin <3.5 g/dL without other obvious cause) will be discussed with supervising specialist for a decision regarding pausing treatment or organising a specialist referral for review without pausing treatment.

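### Arm 2: a redraw after a failed RNA sample can fall on treatment, yet any negative result triggers stop-and-exit with no listed repeat RNA test

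*Protocol article*

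**What the plan says.** All references are to the Protocol article.

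- **Arm 2, Visit 1.** For an eligible participant who is positive at 5 minutes, "the study doctor will provide 28 days of SOF/VEL and the participant will be asked to begin treatment". On timing, "The blood sample for confirmatory RNA testing must be collected prior to providing any treatment medication". For a failed sample, "If there is an issue with the blood sample itself, the participant will be asked to return to the study site as soon as possible", where blood is redrawn. The one supply control is on the next bottle: "Only after confirmatory RNA laboratory results will a second bottle of 28 SOF/VEL doses be provided".
- **Arm 2, Visit 2.** On a negative confirmatory RNA result, "the participant will be asked to stop treatment immediately and to return unused DAAs". A face-to-face visit follows, to explain the result and record the experience of treatment; then, "following this next visit, the participant will exit the study". The rule does not depend on when the sample was drawn, and no repeat RNA test is listed. The same section does use a treatment pause elsewhere: participants with renal dysfunction "will be asked to pause treatment while they seek specialist review".
- **Participant eligibility.** "Must not be currently on or previously had treatment for hepatitis C".
- **Treatment outcome assessment.** RNA is read as SVR only from 4 weeks after the end of treatment.
- **Secondary outcomes.** The overtreated proportion counts people who were prescribed or started treatment and later had a negative RNA result. The SVR comparison covers those confirmed RNA positive. Data monitoring lists the overtreated proportion among the safety end points.

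**The concern.** The rule that blood is drawn before any drug is given protects the first sample only. The redraw sentence applies when that sample has failed. Asking the participant to return implies that they have left, and a fault found by the laboratory would come to light after dispensing. The redraw can then be taken while the participant is on an antiviral.

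A negative result on such a sample does not show that there was no infection at baseline. The visit 2 rule nevertheless acts on it as if it did. An infected person could be told there is no current infection, be stopped part-way through a course, and leave without an SVR test. Read literally, the eligibility criterion would also bar that person from re-enrolling.

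In the analysis the same person is counted as overtreated, becomes a false positive for the 5-minute read, and drops out of the outcomes restricted to RNA-positive participants.

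**Working it through.** No figure in the protocol is in dispute. The check has two parts.

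**1. The rules in sequence**

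- Day 0: blood drawn, 28-day bottle given, participant asked to begin.
- Later: sample found unusable, participant called back. No hold on the drug is stated. The timing is prompt but not fixed. The only firm limit is that the second bottle waits for the RNA result, so up to 28 doses could precede the redraw.
- Redraw negative: stop, return the drug, one visit, exit. No branch for a post-dose sample.
- Other groups do have a route. A test negative at 5 minutes but positive at 20 leads to arm 1 procedures if RNA is positive, and people newly diagnosed with HIV may re-present in Armenia and Tanzania. None covers this group.

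**2. Illustrative size**

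Inputs from the documents: arm 2 targets of 115, 120 and 115 starts, and RNA prevalence among antibody positives of 75%, 30% and 75% (Sample size, Table 3, Armenia, Georgia, Tanzania). Assumed, because the documents give neither: sample failure after dispensing f = 1–5% (central 2%), and share of viraemic redraws undetectable s = 10–50% (central 30%). The Table 3 prevalences are applied to people positive at 5 minutes.

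If the 350 counts RNA-positive starts:

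- Starters: 115/0.75 + 120/0.30 + 115/0.75 = 706.7. RNA negative: 706.7 − 350 = 356.7, or 50.5%.
- Viraemic people wrongly stopped = 350 × f × s. Central: 350 × 0.02 × 0.30 = 2.1. Range: 350 × 0.01 × 0.10 = 0.35 to 350 × 0.05 × 0.50 = 8.75.
- Apparent overtreated share = (356.7 + wrongly stopped)/706.7. Central: 358.8/706.7 = 50.8%. Range: 50.5% to 51.7%.
- Arm 2 uptake, if truly 92%: 350/0.92 = 380.4 viraemic; (350 − 2.1)/(380.4 − 2.1) = 91.96%.
- PPV of the 5-minute read on both arms, if arm 1 yields similar 5-minute positives at 85% uptake: 706.7/0.85 = 831.4 in arm 1, total about 1,538; loss 2.1/1,538 = 0.14 points.

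Other readings give the same picture:

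- With the 62% PPV cited in the Background: 350/0.62 = 564.5 starters, 214.5 negative (38.0%), becoming 216.6/564.5 = 38.4%.
- If 350 is all starters: RNA positive 115 × 0.75 + 120 × 0.30 + 115 × 0.75 = 208.5; wrongly stopped 208.5 × 0.02 × 0.30 = 1.25; share 141.5/350 = 40.4% becomes 142.75/350 = 40.8%.

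**Does excluding post-dose samples repair the overtreated share?** Only if failure is unrelated to country and RNA status. Take failure of 5% in Georgia and 1% elsewhere, with s = 30%:

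- Exclude all post-dose samples: (280 × 0.95 + 76.7 × 0.99)/(400 × 0.95 + 306.7 × 0.99) = 341.9/683.6 = 50.0%.
- Leave the data alone: extra negatives (120 × 0.05 + 230 × 0.01) × 0.30 = 2.5; (356.7 + 2.5)/706.7 = 50.8%.
- True value 50.5%. Exclusion misses by about 0.5 points, leaving alone by about 0.35.

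Exclusion therefore belongs in a sensitivity analysis. Best and worst cases for post-dose negatives at f = 2%, s = 30%: (356.7 × 0.98)/706.7 = 49.5% if all were truly viraemic, 50.8% if none were.

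**The case against.** The strongest reply is that this is a condensed article. It states the rule that matters, blood before drug, and asks for a prompt redraw. Whether dosing is held and whether RNA is repeated may be set out in the full protocol or in site procedures. The visit 2 rule may also have been written with the pre-dose sample in mind, and a fault noticed before dispensing does no harm. This limits confidence but does not remove the point: the published rules, followed as written, lead to a definite wrong action, and the negative-result rule is a directive with no stated discretion.

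The reply is right about size. Both drivers are assumed. The 28 doses are a supply limit, not an expected delay. A reader might infer that the overtreated proportion or the uptake comparison is materially biased; the documents give no failure rate or speed of RNA decline to support that, and under the assumed ranges the shifts are small.

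A reader might also infer that the person loses all access to treatment. The documents do not support that. The bar applies to this study. The Study setting section describes free RNA testing and treatment in Armenia, a national elimination programme in Georgia, and free treatment in Tanzania, although RNA testing there costs the patient about US$70. Visit 2 also provides for active follow-up and a discussion of window periods.

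Finally, a pause interrupts same-day treatment for those affected, and the trial is already recruiting under several ethics committees. Both are real costs, though small.

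**Conclusion.** The point holds as a minor patient-safety clarification. As published, arm 2 allows an RNA redraw on treatment and lets a negative result from it end treatment and participation in this study. The protocol elsewhere reads post-treatment RNA as an outcome only from 4 weeks off drug.

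The number affected cannot be derived from the documents. Under the assumed rates it is about 2 viraemic participants (range 0.4 to 9), and the overtreated share moves by about 0.3 points, which is negligible for pooled results. Those figures assume that the Table 3 prevalences apply to people positive at 5 minutes, and that failure is equal across countries and unrelated to RNA status. Confidence is medium, because the full protocol may already hold the drug or repeat the test.

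**What to change.** 1. **Arm 2, Visit 1.** When a sample is found unusable after dispensing, contact the participant at once not to start, or to pause, until the redraw, which should be taken promptly. A pause is already used for renal dysfunction, and the Visit 3 section already lets missed doses be made up.
2. **Arm 2, Visit 2.** A negative result on a sample taken after the first dose does not by itself end participation. Keep the drug off and repeat RNA at 4 or more weeks off drug before exit. If positive, offer treatment by arm 1 procedures despite the earlier doses.
3. **Analysis.** Flag each RNA sample as before or after the first dose; self-reported first-tablet timing is already collected. Keep the main overtreated and accuracy analyses as planned. Report a sensitivity analysis that excludes post-dose samples, with best- and worst-case bounds, also by country. A negative repeat should not be read as proof of no baseline infection, since a short course may have cured it.

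**Cost.** Short pauses or delayed starts for 706.7 × 0.01 = 7 to 706.7 × 0.05 = 35 starters. Repeat tests = 356.7 × f + wrongly stopped: central 7.1 + 2.1 = 9.2, range 3.9 to 26.6, and fewer if the hold in step 1 works. At US$10–38 a test (Background), or the US$70 Tanzanian patient price applied to all, the central test cost is US$92 to about US$646. Add the extra visits and tracing at least 4 weeks after stopping, and a minor amendment communicated to the Alfred, WHO and country ethics committees.
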